# Outcomes

1. Primary outcome is number of AF-episodes during and after the exercise intervention measured on handheld ECG (Zenicor®)
2. Secondary outcomes are:
3. time to first AF-episode
4. change in maximal physical capacity measured on Six Minute Walk Test and ergometer bike
5. change in heart rate, blood pressure and cardiac load measured on echocardiography
6. change in quality of life
7. Tertiary outcomes are:
8. Number of hospital admissions with AF or complications to AF
9. Death
10. Change in biochemical markers

# Statistical analyses

Patient characteristics and baseline data will be analyzed using descriptive statistics. Parametric data will be reported as mean and standard deviation (SD), non-parametric data as median and range. Depending on the distribution, student-t-test or non-parametric tests will be used when comparing the intervention groups.

The effect of exercise will be analyzed in several ways depending on outcome variable; burden of AF and hospital admissions are analyzed by Poisson regression analysis, survival analyses (time-to-event) using Kaplan-Meier plots and hazard regression analysis. All analyses will be adjusted for common cardiac comorbidities and reported with two-sided confidence intervals. A p-value < 0.05 is considered statistically significant.

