## Assessment of outcome

Burden of AF:

By using a handheld ECG device (Zenicor®), the patients transmits an ECG twice daily and in case of symptoms of arrhythmia. An episode of AF is defined as > 10 seconds with irregular frequency and no visible p-waves on ECG. Total number of AF-episodes and time to first AF-episode is registered.

One year after last the exercise session, all hospital admissions related to AF are registered from the medical records; recurrent AF, cardiac failure, stroke, dysregulated antithrombotic treatment or medical side effects, implantation of pacemaker, and surveillance of medical treatment.

Quality of Life:

At baseline and at 12-week follow up the quality of life is assessed using the Short Form 36 (SF36) and European Heart Rhythm Association score (EHRA-score).

Patient characteristics:

Age, gender, ethnicity, BMI, comorbidity, medication, cardiac risk profile (family history, smoking, hypertension, hypercholesterolemia, diabetes, stroke/TCI, claudicatio intermittens, daily physical activity, blood pressure and heart rate.

Physical capacity:

Physical capacity is measured on Six Minute Walk Test and assessment of efficiency on ergometer bike with continuously monitoring of blood pressure and ECG. A ST-depression on ECG is considered significant if it is depressed by 0.1 mV measured 60 ms after the QRS-complex. The ergometer test is considered complete when reaching 85% of maximal expected heart rate.

Cardiac load:

Blood pressure and heart rate are measured for 24 hours at baseline and 12-week follow up. Blood pressure will be reported as mean systolic and diastolic blood pressure during daytime and night time, respectively. Heart rate will be reported as mean, minimum and maximum heart rate, arrests, supraventricular and ventricular ectopic activity and number of AF-episodes.

Echocardiography is reported with standard estimates in accordance with national guidelines. Additionally, left atrium volume (ml/m^2^) will be assessed as well as diastolic function (e’, a’ and E/e’).

Biochemical and genetic markers:

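### For the continuous change outcomes the only named method that fits is a t-test or rank test, which cannot carry the stated comorbidity adjustment, and that adjustment omits the outcome's own baseline value

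*Protocol*

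**What the plan says.** Protocol, Outcomes. The secondary outcomes include "change in maximal physical capacity measured on Six Minute Walk Test and ergometer bike", "change in heart rate, blood pressure and cardiac load measured on echocardiography" and change in quality of life. Change in biochemical markers is tertiary.

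Protocol, Assessment of outcome. "Blood pressure and heart rate are measured for 24 hours at baseline and 12-week follow up", and SF36 and the EHRA-score are assessed at the same two times. The Methods section places blood sampling at baseline and after the 12 weeks, and the walk test and ergometer test at baseline. For the walk test, ergometer and echocardiography, the follow-up measurement is implied by the word change; the study figure is not shown.

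Protocol, Statistical analyses. The first paragraph opens with patient characteristics and baseline data and ends by saying that, according to how the data are distributed, "student-t-test or non-parametric tests will be used when comparing the intervention groups". The second paragraph turns to the effect of exercise: "burden of AF and hospital admissions are analyzed by Poisson regression analysis, survival analyses (time-to-event) using Kaplan-Meier plots and hazard regression analysis". It names no model for a continuous change. It then states: "All analyses will be adjusted for common cardiac comorbidities and reported with two-sided confidence intervals".

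**The concern.** A t-test or rank test has no place for covariates. If it is the method for the change outcomes, the promise that all analyses are adjusted cannot be kept for them. The adjustment set is also incomplete where it would matter most. For a measurement taken before and after treatment, the baseline value is usually the strongest predictor of the follow-up value, and it is not listed.

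At stake are the precision and the conditional accuracy of most secondary results and one tertiary result, in a trial of 60 patients. Change scores carry regression to the mean: an arm that by chance starts lower tends to improve more, whatever the exercise intensity does.

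**Working it through.** **Which method applies.** Poisson regression is assigned to AF burden and admissions, and Kaplan-Meier and hazard regression to time-to-event data. None of these fits a continuous change. The t-test/rank-test sentence is the only remaining candidate. It can be read in two ways:

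- *Broad reading* (it covers any comparison of the arms): the change outcomes get an unadjusted test, which conflicts with the sentence that all analyses are adjusted.
- *Narrow reading* (it covers baseline data only): there is no conflict, but the change outcomes have no named method.

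On both readings the adjustment set stated for all analyses leaves out the baseline value.

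**Inputs.** The total is 60 patients (Methods). Envelopes A and B are in equal numbers, so there are 30 per arm. The protocol gives neither an SD nor a baseline–follow-up correlation ρ for any change outcome, so ρ is assumed over 0.3 to 0.9. It also states no power or precision figure for these outcomes, so there is none to reproduce.

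**Precision.** Take equal variances σ² at both times and express variances in units of σ²:

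- change score: 2(1−ρ)
- ANCOVA: 1−ρ² = (1−ρ)(1+ρ)
- ratio, change score to ANCOVA: 2/(1+ρ)

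Patients that ANCOVA needs to match 60 analysed by change score: 60(1+ρ)/2. Power of ANCOVA at an effect for which the change-score test has 80% power: Φ(2.802·√(2/(1+ρ)) − 1.960), where 2.802 = 1.960 + 0.842.

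| ρ (assumed) | Change-score variance | ANCOVA variance | Ratio | Patients to match 60 | ANCOVA power |
|---|---|---|---|---|---|
| 0.3 | 1.40 | 0.91 | 1.54 | 39 | 93.5% |
| 0.5 | 1.00 | 0.75 | 1.33 | 45 | 89.9% |
| 0.7 | 0.60 | 0.51 | 1.18 | 51 | 86.0% |
| 0.8 | 0.40 | 0.36 | 1.11 | 54 | 84.0% |
| 0.9 | 0.20 | 0.19 | 1.05 | 57 | 82.0% |

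Estimating the baseline slope costs a factor of about 1 + 1/56 = 1.018. The ANCOVA/change-score variance ratio then moves from 0.65 to 0.662 at ρ = 0.3, and from 0.95 to 0.967 at ρ = 0.9. The gain remains over the whole range.

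**Baseline imbalance.** With 30 per arm, the chance difference in baseline means has SD √(2/30) = 0.26 baseline SDs, with a 95% range of ±1.96 × 0.258 = ±0.51. Given an observed difference D, the follow-up means are expected to differ by the treatment effect plus ρD. The change score subtracts the whole of D. Its conditional error is therefore ρD − D = −(1−ρ)D. For D = 0.5 SD this is −0.25 SD at ρ = 0.5, −0.15 SD at ρ = 0.7 and −0.05 SD at ρ = 0.9. ANCOVA subtracts ρD and removes this error.

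**The case against.** The strongest objection is textual. The t-test sentence belongs to a paragraph about baseline data, and the treatment effect is taken up only in the next one. Nothing assigns a t-test to the change outcomes. On that reading the two sentences do not conflict, and naming a model for continuous outcomes is something a protocol commonly leaves to its statistical analysis plan, which is not shown here. The first part stands: the use of the t-test for these outcomes is an inference and must be called one. The second part does not dispose of the point. The protocol did not stay silent on covariates; it stated an adjustment set for all analyses, and that set lacks the baseline value.

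A second objection is that a change-score comparison is a legitimate analysis. This also stands. A reader might infer that the exercise effects would be biased, or that baseline imbalance would go uncorrected. The documents support neither. Randomisation makes the change-score contrast unbiased on average, and the change score does use the baseline. The fault is over-correction in the sample at hand. Imbalance would be left wholly uncorrected only if follow-up values alone were compared, and the outcomes are defined as changes.

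Third, the size of the loss depends on an unknown ρ and is small when ρ is high. The formula assumes equal variances and a comparison of means, so it does not describe a rank test or the ordinal EHRA-score. All of this stands and limits what can be claimed.

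**Conclusion.** The point holds for the continuous change outcomes: walk test, ergometer capacity, 24-hour blood pressure and heart rate, echocardiography, SF36 and biomarkers. Their analysis is either a test that cannot carry the stated adjustment or is not named, and in both cases the baseline value is missing from the adjustment set.

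A change-score comparison then has 1.54 to 1.05 times the variance of ANCOVA for ρ from 0.3 to 0.9, which is as if 39 to 57 of the 60 patients would have sufficed. These figures rest on an assumed ρ, equal variances and 30 analysed per arm.

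It would go too far to say that every secondary outcome loses precision. Time to first AF-episode is secondary and is not a change. The primary AF count is not touched either: handheld recording is described only during the intervention and for two months after it, so no pre-randomisation count is described to adjust for. This is an avoidable inefficiency and an unclear rule, not an invalid analysis.

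**What to change.** In the protocol's Statistical analyses section:

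- For each continuous outcome measured at baseline and follow-up, analyse the 12-week value in a linear model (ANCOVA) on arm, with that outcome's baseline value as a prespecified covariate together with the comorbidities already intended. Report the adjusted difference with its two-sided 95% confidence interval. Use a log-transform or a bootstrap interval if the data are skewed.
- For the EHRA-score, use an ordinal regression model with the baseline class as covariate.
- Restrict the t-test/rank-test sentence to descriptive comparisons, which also removes the conflict with the adjustment sentence.

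The cost is wording only. The baseline measurements are already part of the design, and no patient, visit or test is added. The change should be fixed before outcome data are compared by arm.

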# Sample size

The aim of our trial is to study whether high intense physical exercise reduces burden of AF more than low intense physical exercise. Our primary outcome, burden of AF, is assessed as total number of ECGs with AF. We expect to reduce the burden of AF with 25%. The patients send an ECG twice daily and in case of symptoms which will sum up to 300 ECG per patient. We assume that total number of ECGs with AF in the low intense group will be 20 compared to 15 in the high intense group. The estimated power will be 94.3% for α=0.05 (two-sided 95% CI) and SD=6, which is higher than the generally accepted power of 80%.

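### Poisson regression is named for the primary AF count with no provision for overdispersion, although the planning SD of 6 implies a variance 1.8 to 2.4 times the Poisson variance

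*Protocol*

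**What the plan says.** In the Protocol, Statistical analyses, the sentence on the effect of exercise states that "burden of AF and hospital admissions are analyzed by Poisson regression analysis". The section's only further instruction for these models is covariate adjustment: "All analyses will be adjusted for common cardiac comorbidities and reported with two-sided confidence intervals". The comorbidities are not listed. No scale parameter, robust variance, negative binomial alternative or dispersion check is mentioned.

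The Protocol, Sample size, identifies the outcome and its planning values. "Our primary outcome, burden of AF, is assessed as total number of ECGs with AF". The expected values are "total number of ECGs with AF in the low intense group will be 20 compared to 15 in the high intense group", and "The estimated power will be 94.3% for α=0.05 (two-sided 95% CI) and SD=6".

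**The concern.** Poisson regression takes the variance of the count, given the covariates, to equal its mean. The default standard errors depend on that equality. The protocol's own planning values break it, at least before covariate adjustment: a variance of 36 goes with means of 20 and 15.

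If the named model is run with its default errors, the standard error of the log rate ratio is too small, the confidence interval is too narrow and the primary p-value is too small. In a trial of 60 patients, a difference produced by ordinary between-patient variation could then be reported as an effect of exercise intensity.

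**Working it through.** **Inputs**
- Means of 20 (low intensity) and 15 (high intensity), SD 6, two-sided alpha 0.05: Protocol, Sample size.
- 60 patients, with the two letters equally distributed among the envelopes, so 30 per arm: Protocol, Methods.
- Model: Poisson regression: Protocol, Statistical analyses.

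**1. The plan's own figure, and what SD 6 means in it.** For a comparison of means, the standard error of the difference is 6 × sqrt(2/30) = 1.549, and 5/1.549 = 3.227. With the one-sided 5% critical value, power is Phi(3.227 − 1.645) = 94.3%, which is the stated figure. With the two-sided value it is Phi(3.227 − 1.960) = 89.7%. That the stated power matches the one-sided calculation is a separate matter. What counts here is that the figure is reproduced when SD 6 is taken as the between-patient SD of the count with 30 per arm.

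**2. Dispersion implied by the planning values.** phi = SD²/mean.

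| Mean | Poisson SD | phi = 36/mean | Standard error too small by sqrt(phi) |
|---|---|---|---|
| 20 | 4.47 | 1.80 | 1.34 |
| 17.5 | 4.18 | 2.06 | 1.43 |
| 15 | 3.87 | 2.40 | 1.55 |

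For example, with both arms at mean 20, each arm totals 30 × 20 = 600. The default standard error of the log rate ratio is sqrt(1/600 + 1/600) = 0.0577. With SD 6 it should be 0.0577 × 1.342 = 0.0775.

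**3. True size of the nominal 5% test, no covariate effect.** Size = 2 × [1 − Phi(1.96/sqrt(phi))]. This was checked by simulating negative binomial counts with SD 6 and a common mean, 30 per arm, 100,000 runs.

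| Common mean | Size by formula | Simulated, unscaled | Simulated, Pearson-scaled |
|---|---|---|---|
| 20 | 14.4% | 14.4% | 5.0% |
| 17.5 | 17.2% | 17.3% | 5.0% |
| 15 | 20.6% | 20.7% | 5.1% |

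The coverage of a nominal 95% interval is one minus the size: about 86% at mean 20 and about 79% at mean 15.

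**4. Allowing for covariates.** If the comorbidities explain a share r of the excess, phi becomes 1 + (36/mean − 1)(1 − r). The values of r are assumptions; the protocol gives none.

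| r | Size at mean 20 | Size at mean 15 |
|---|---|---|
| 0 | 14.4% | 20.6% |
| 0.25 | 12.1% | 17.1% |
| 0.50 | 9.8% | 13.3% |
| 0.75 | 7.4% | 9.2% |
| 1 | 5.0% | 5.0% |

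**5. Power after the correction.** For 20 versus 15 with SD 6 and 30 per arm, the Pearson-scaled test with a t reference on 58 degrees of freedom has simulated power of 88.1%. The unscaled test shows 96.8%, but that is not power at a 5% level.

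**The case against.** The strongest objection is that the protocol names a model and not a variance estimator. Poisson regression with a scale factor or sandwich errors is still Poisson regression, and a statistical analysis plan, not shown here, may specify it. That stands. A reader might infer that the protocol commits to unscaled errors, but this rests on silence alone. What remains is that the protocol names a model whose default form does not fit the figures in its next section, and says nothing to reconcile the two.

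Second, SD 6 is an unadjusted planning value, whereas the Poisson assumption is conditional on covariates. This also stands: the figures with r = 0 are upper values for SD 6. Adjustment brings the size back to 5% only if the comorbidities explain all of the excess.

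Third, size is defined under a common mean. The protocol's comparator mean is 20, so about 14% is the natural figure. A reader might take 14% to 21% as a range the protocol predicts, but the upper end needs both arms to average 15, a value assigned only to the high-intensity arm under the expected effect.

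Fourth, a reader might infer still larger inflation, since successive ECGs within one spell of AF are unlikely to be independent and admissions recur within patients. That is plausible, but the protocol gives no SD other than 6 for the AF count and no variance at all for admissions, so neither can be given a figure.

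The same section also mentions t-tests and non-parametric tests for comparing the groups. The sentence on the effect of exercise is the more specific one, and it assigns AF burden to Poisson regression.

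**Conclusion.** The point holds in a conditional form. On the protocol's own planning values, the AF count is overdispersed by a factor of 1.8 to 2.4 relative to the model named for it, and nothing in the protocol deals with this. With default Poisson errors the primary test would have a size of about 14% at the comparator mean of 20 (about 21% if both arms averaged 15) instead of 5%.

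These figures assume that SD 6 is the between-patient SD of the count of ECGs with AF, that follow-up is equal, that there are 30 patients per arm and that the covariates explain none of the excess. If they explain a quarter to three quarters of it, the size is about 7% to 12% at mean 20 and 9% to 17% at mean 15.

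The documents do not show that unscaled errors will in fact be used. Nor do they support the inference that the trial loses adequate power once the analysis is corrected: about 88% is above the 80% benchmark that the Sample size section cites.

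**What to change.** In the Protocol, Statistical analyses, state that the AF count will be analysed by negative binomial regression, or by Poisson regression with a Pearson scale factor or robust (sandwich) standard errors, and that the rate ratio will be reported with the corresponding 95% interval. Choose one of these before the data are seen. The figures above were checked for the Pearson-scaled version with a t reference; the other two were not simulated here. If a statistical analysis plan already specifies such a method, aligning the protocol's sentence with it is enough.

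Use the same method for admission counts as a precaution, without attaching a figure to the expected inflation.

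The cost is one sentence and wider intervals. No additional patients or data are needed, and power under the planning values is about 88%.

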# Methods

The study is an assessor blinded, randomized controlled trial. Patients are randomized by simple drawing. For logistic reasons, an exercise team consists of ten patients. The letters A and B are equally distributed in 20 envelopes, and represents the physical exercise intensity. The sealed envelopes are all put into a larger envelope from where the patients will draw one envelope at randomization.

[figure not shown]
A total of 60 patients with paroxysmal/persistent AF will be included, using consecutive sampling, from the Department of Cardiology, Copenhagen University Hospital Hvidovre. After inclusion, baseline tests will be performed as follows: physical capacity measured on Six Minute Walk Test and maximal physical capacity measured on ergometer bike, Figure 1. Patient characteristics, medication, risk factors and comorbidity will be registered. Before the exercise intervention, all participants will complete a nurse-led rehabilitation program regarding AF. The patients will then be randomized to either low intensity physical exercise (50% of maximum physical exertion) or high intensity physical exercise (75-85% of maximum physical exertion).

The exercise intervention lasts 12 weeks with exercise sessions twice weekly of 60 and 90 minutes duration, respectively. They consist of cardiovascular exercise (cycling, running) and will be supervised by cardiac physiotherapists. Intensity is measured as perceived exertion on Borg 20 scale introduced at the initial sessions. The exercise sessions will be conducted at the hospital.

During the intervention and two months after the last exercise session, the patients upload an electrocardiogram (ECG) from a handheld ECG-device twice daily and in case of symptoms of AF.

One year after the intervention is completed the patients will be invited to a follow-up. During the follow-up time all hospital admissions are registered from the medical records.

At baseline and after the 12-week intervention, blood samples will be taken and stored in a bio bank for later analyses. A total of 90 mL. blood per participant will be drawn. The blood samples will be stored anonymously at minus 80 degrees Celsius for 10 years for future research.

The trial is expected to start in October 2012 with end of follow-up one year after the last exercise session.

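### The SD of 6 behind the stated power has no source and leaves little room for sustained AF, and the Poisson model named for the primary outcome adjusts for neither AF type nor baseline AF

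*Protocol*

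**What the plan says.** - **Population.** Protocol, Methods: "A total of 60 patients with paroxysmal/persistent AF will be included". The exclusion criteria remove permanent AF only, so persistent AF stays eligible. The expected share of persistent AF is not given.
- **Allocation.** Protocol, Methods: "The letters A and B are equally distributed in 20 envelopes". Patients draw from these, and no stratification by AF type is described.
- **Outcome.** Protocol, Sample size: "Our primary outcome, burden of AF, is assessed as total number of ECGs with AF", with about 300 ECGs per patient. Protocol, Assessment of outcome: "An episode of AF is defined as > 10 seconds with irregular frequency and no visible p-waves on ECG". The Outcomes section names the number of AF episodes.
- **Power.** Protocol, Sample size: 20 against 15 ECGs with AF, "α=0.05 (two-sided 95% CI) and SD=6", power 94.3%. No source is given for the SD.
- **Analysis.** Protocol, Statistical analyses: Poisson regression for the burden of AF, and "All analyses will be adjusted for common cardiac comorbidities and reported with two-sided confidence intervals".
- **Baseline data.** AF type is not among the listed patient characteristics. Handheld recording starts with the intervention, so the outcome has no baseline value. The 24-hour recording at baseline does report "supraventricular and ventricular ectopic activity and number of AF-episodes".

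**The concern.** The count can run from 0 to about 300, and the trial mixes two kinds of patient. Someone with paroxysmal AF may show AF on a few tracings. Someone with persistent AF may show it on long unbroken runs. An SD of 6 around a mean of 20 describes a fairly uniform group.

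If even a few patients have sustained AF, three things follow. The true SD is well above 6 and the power well below the stated figure. With unstratified allocation, the arm means can differ by more than the planned 5 ECGs by chance alone. And the model as named has no term for the characteristic that drives this variation, while its variance equals the mean, so it would treat a chance imbalance as firm evidence.

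**Working it through.** **Inputs.** From the protocol: 60 patients (30 per arm), means 20 and 15, SD 6, two-sided α 0.05, about 300 ECGs per patient, two scheduled ECGs a day. Assumed here: how many patients have sustained AF, and for how long.

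**1. The stated power.** The standard error is 6 × √(2/30) = 1.549, and 5/1.549 = 3.227.
- Two-sided: Φ(3.227 − 1.960) = 89.8% (88.8% by the noncentral t).
- One-sided: Φ(3.227 − 1.645) = 94.3%.

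The stated 94.3% is therefore the one-sided figure, although the text says two-sided.

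**2. What an SD of 6 allows.** In a sample of n, no value can lie more than (n − 1)/√n × SD from the mean: 29/√30 × 6 = 31.8. With a mean of 20 the ceiling is about 52 AF ECGs, which is 26 days of sustained AF at two ECGs a day.

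**3. One patient per arm with sustained AF.** For the first two rows the other 29 patients have mean 20 and SD 6. The arm SD is √[(29 × 36 + (x − 20)² × 29/30)/29]. In the last row the arm mean is held at 20, so the others average (600 − 300)/29 = 10.3. Power is from a two-sided t-test for a difference of 5, with that SD in both arms.

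| AF ECGs in that patient | Arm SD | Power |
|---|---|---|
| 56 (4 weeks) | 8.9 | 57% |
| 112 (8 weeks) | 17.8 | 19% |
| 300 (throughout) | 53.2 | 6.5% |

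**4. Power by SD alone (t-test).** SD 6: 89%. SD 10: 48%. SD 20: 16%.

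**5. Shift in an arm mean.** Replacing one average patient by one in AF throughout moves the mean by (300 − 20)/30 = 9.3 or (300 − 15)/30 = 9.5 ECGs, nearly twice the planned difference.

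**6. The Poisson variance.** Even the protocol's own SD exceeds what a Poisson model implies: 36/20 = 1.8 and 36/15 = 2.4 times the mean. At a ratio of 1.8, a nominal 5% test uses an effective cut-off of 1.96/√1.8 = 1.46, so it rejects a true null about 14% of the time. In simulation with 3% of patients in AF on all 300 ECGs and no adjustment for AF type, this rises to 73%.

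**7. What adjustment does.** Illustrative mix: 20% persistent averaging 60 AF ECGs and 80% averaging 10 (0.2 × 60 + 0.8 × 10 = 20), with variance twice the mean within each type. Ranges are across repeated simulations.

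| | Unadjusted | Adjusted for AF type |
|---|---|---|
| Plain Poisson, true null rejected | 67–69% | 16–17% |
| Quasi-Poisson, power at ratio 0.75 | about 15–20% | 87–90% |

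With no treatment effect, the arm means in this mix differ by more than 5 ECGs in about a third of trials.

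The mix is favourable to adjustment, because persistent patients are given an SD of only √120 ≈ 11. If their counts vary widely (SD about equal to the mean, capped at 300), adjusted plain Poisson rejects a true null in 71% of trials and adjusted quasi-Poisson in 24%.

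**The case against.** - **The share of patients in sustained AF is unknown.** This stands. A reader might infer that an SD of 6 is impossible, or that a few persistent patients are bound to decide the primary result. The documents do not support that: they give neither the share of persistent AF nor how many patients would stay in AF through the recording window. The claim needs at least one patient per arm with about four weeks of AF or more.
- **Continuous AF might count as one episode.** The Outcomes section speaks of episodes, and merging consecutive tracings would shrink the problem sharply. But the Sample size section states the outcome as ECGs with AF, and no merging rule is given. The point therefore applies to the outcome as powered.
- **Covariates belong in the SAP.** In part. A SAP may add covariates or a dispersion term, and their mere absence would be no finding. But the protocol itself states an adjustment set for all analyses, the Poisson model and the SD of 6.
- **AF type is not a listed baseline item.** Correct. A reader might suppose that it is already collected. Eligibility needs only documented AF that is not permanent. The type should be classifiable from the history used for that exclusion, but it has to be recorded.
- **The 24-hour episode count is a weak covariate.** Partly right: unbroken AF could score as one episode. The recording can still show who was in AF at baseline if it is coded that way.
- **Under the named model the damage is not mainly lost power.** This stands. Plain Poisson regression keeps rejecting, but without a sound basis. Power is lost once the variance is estimated honestly. Covariates alone do not cure this.

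**Conclusion.** The concern holds conditionally. The SD of 6 is unsourced and fragile in a population that includes persistent AF. One patient per arm with about four weeks of sustained AF takes two-sided power from 89% to about 57%, and longer spells take it much lower. This assumes that each AF tracing counts, 30 patients per arm and no dropout.

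The stated adjustment leaves out AF type and baseline AF, so a chance imbalance of one or two patients in sustained AF can exceed the 5-ECG target. With the plain Poisson variance this becomes a false-positive problem, which the protocol's own SD already implies at about 14%. The larger simulated rates depend on assumed mixes and show direction and scale only.

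It would go too far to say that the trial cannot reach adequate power, or that adding AF type alone would restore it. Separately from the mix of patients, 94.3% is a one-sided figure in a two-sided plan.

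**What to change.** 1. Record AF type (paroxysmal or persistent) at baseline.
2. Add AF type and AF on the baseline 24-hour recording to the primary model, alongside the comorbidities and not in their place. Code the recording as AF present or share of time in AF, rather than only as a number of episodes.
3. Specify a variance that allows for overdispersion, such as a negative binomial model or robust standard errors suited to 60 patients. A single scale factor may not be enough if the two AF types differ greatly in spread.
4. Replace the 94.3% with two-sided power over a range of SDs: about 89% at SD 6, 48% at SD 10 and 16% at SD 20. Give the source of the SD, or say that it is an assumption.
5. State in one place whether consecutive AF tracings count singly or as one episode, because the SD depends on it.

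The cost is one added baseline item, changes of wording in the analysis and sample-size sections, and a less favourable stated power.
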